#### Data analysis

We will monitor primary and secondary endpoint outcomes throughout the 5-year study period (Fig. 3); data analysis will be conducted in year 5. The difference in clinical malaria incidence between treatment and control groups will be compared using Poisson multivariate regression models with intervention, age, and calendar time as covariates, using a generalized estimating equations (GEE) approach. GEE is necessary since incidence will be modeled monthly as a temporally-correlated repeated measure using grouped data. Intervention will be a time-varying covariate since the treatment crosses over after three intervention rounds. Since there is no intervention in the 8 months during the washout period, interval censoring will be performed to exclude the second 4 months of data during this period. The odds ratio and the 95 % confidence interval for clinical malaria rates between treatment and control groups will be calculated. Difference in vector density and EIR will be analyzed using a negative binomial regression model and the GEE approach. In all these analyses, clusters will be indicated as intervention and control, calendar time will be categorized into: pre intervention, intervention, postintervention (4 months), washout (4 months), crossover intervention, postintervention (4 months), and nonintervention, and months since intervention (for both first intervention and crossover) will also be included as an independent variable. These variables will allow for comparison between intervention and control clusters based on baseline observations, e.g., relative reduction in vector density, and allow for evaluation of cumulative effect, e.g., the second round of treatment may produce added-effect following first-round treatment [49, 60, 61].

Finally, for the economic evaluation, we will calculate incremental cost-effectiveness ratios (ICERs) based on the primary endpoint (clinical malaria cases prevented) and on long-term health outcomes including malaria deaths averted. Using the “ingredients approach” [62, 63], costs will be classified according to: initial setup investment (e.g., capital for vehicles used in transporting larvicides, GPS units for habitat mapping, storage space and equipment, and traps for mosquito surveillance), running costs (e.g., long-lasting larvicides, salary for larvicide application staff, staff training, protective clothes, gloves, fuel costs, and vehicle insurance), and costs of program management and quality control (e.g., material procurement, project coordinator, and quality controller). Cost data will be estimated from health facility and Ministry of Health records, LLML manufacturers and financial accounts of the research project. One-way and multi-way sensitivity analysis will be undertaken to examine the implications of potential changes in variables such as larvicide price and larviciding application frequency. ICERs will be reported from both provider and societal perspectives for different transmission intensity scenarios.

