Using these data, each cluster will be allocated to either treatment or control through randomization using the following procedures. First, each of the four parameters listed above will be standardized with the highest cluster as 1. Second, we will assign the highest weight for clinical malaria cases (weight = 5), the lowest weight for human population size (0.5), and intermediate weights for expected vector density (2) and larval habitats (2), following the method of Corbel et al*.* [58]. For each cluster a rank score will be computed as the sum of weighted clinical malaria incidence, vector density, habitat abundance, and human population size. Finally, the 14 clusters within each county will be sequentially numbered according to their rank scores and sorted into seven blocks of two clusters having successive rank scores. We expect the two clusters within each block to have similar risk characteristics for clinical malaria, vector abundance, larval habitats, and human population size. In each block, the ranks of the two clusters are put into two sealed envelopes, one cluster will be randomly allocated to treatment and another to control, using computer-generated random numbers (0 – control, 1 – intervention).

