#### Sample size justification

Sample size was calculated based on 2010 and 2011 active case surveillance results from Iguhu and Emutete areas [47]. Then the number of clusters required and the number of individuals required for each cluster were calculated following the methods developed by Hayes and Bennett based on cluster-randomized trials assuming equal population for each cluster [59]. The observed malaria incidence rate was 52.7 cases per 1000 people year in 2011. We calculated the numbers of clusters (matched-pairs) and individuals required for epidemiological (clinical malaria) assessment of the long-lasting larvicide treatments to detect a 50 % protective efficacy conferred by the treatment compared with the reference group (no treatment), with a power of 80 %, significance level of 5 % and the coefficient of variation of true proportions between clusters within each treatment was assumed to be 0.15. The estimated number of clusters (matched-pairs) for the intervention will be five and the required number of individuals for each matched-pair will be 1196; assuming a design effect of 0.25 and 20 % of subjects lost to follow-up. The estimated number of clusters (matched-pairs) for the intervention will be seven and the required number of individuals for each of the matched-pairs will be fewer than 2000. The 28 clusters proposed in the randomized cluster study will detect 50 % malaria incidence reduction with 99.9 % power and 30 % incidence reduction with 85.3 % power. This is based on the current malaria incidence rate in the study sites (52 clinic cases per 1000 population year) and a two-tailed alpha with a human population size of 2000 per cluster (Table 1). If the malaria incidence is 50 % lower than the current value, the design will still detect 50 % incidence reduction with 99.7 % power and 40 % reduction with 95.2 % power (Table 1).

**Table 1 Tab1:** Calculated power (%) to detect various levels of incidence reduction under three incidence scenarios

Annual incidence rate (cases/1000 population)	Malaria incidence reduction			
	50 %	40 %	30 %	20 %
Observed in the site: 52	99.9	98.7	85.3	48.6
Low-incidence value: 26	99.7	95.2	74.4	38.9
High-incidence value: 78	99.9	99.3	89.0	53.0

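### Clusters are randomised and sized as matched pairs within county, but the stated GEE models contain no pair or county term, so the analysis does not follow the design

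*Protocol article*

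**What the plan says.** **Randomisation (Protocol article, Randomization).** The 14 clusters in each county are ranked on a weighted score and sorted into seven blocks of two with adjacent ranks. One cluster per block is allocated to larvicide, which gives 14 matched pairs nested in two counties. The stated reason is "We expect the two clusters within each block to have similar risk characteristics for clinical malaria, vector abundance, larval habitats, and human population size".

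**Sample size (Sample size justification).** The calculation is matched: "We calculated the numbers of clusters (matched-pairs) and individuals required for epidemiological (clinical malaria) assessment". Its inputs include "significance level of 5 % and the coefficient of variation of true proportions between clusters within each treatment was assumed to be 0.15".

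**Analysis (Data analysis).** The primary model is "Poisson multivariate regression models with intervention, age, and calendar time as covariates, using a generalized estimating equations (GEE) approach". Intervention is time-varying because the arms cross over. For all models, including those for vector density and EIR, the section adds an intervention/control indicator, categorised calendar time and months since intervention. Pair, block and county are not in the list. The section names no variance estimator, working correlation or reference distribution.

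**The concern.** Randomisation and sample size treat the pair as the unit within which treatment is compared. The analysis treats the 28 clusters as unrelated apart from arm and calendar period.

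When two clusters of a pair move together over time, for example through shared rainfall, vector pressure or net coverage, the treatment contrast is less variable than an unpaired standard error assumes. The precision bought by pairing is then lost and the intervals are wider than they need be.

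When the pairs share nothing over time, the unpaired analysis loses nothing. Its error rate then depends on how the sandwich errors are handled with 28 clusters. The calibration of the primary test thus rests on two things the article does not fix: the within-pair correlation over time and the variance estimator.

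**Working it through.** **1. The plan's own figure, to confirm that the sample size is matched.** Inputs from Sample size justification: control rate λ0 = 0.052 ("52 clinic cases per 1000 population year"), λ1 = 0.7 × 0.052 = 0.0364, k = 0.15, y = 2000, two-sided 5 % ("two-tailed alpha with a human population size of 2000 per cluster"). The Hayes-Bennett matched formula for c pairs is

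c = 2 + (z_α/2 + z_β)² × [(λ0 + λ1)/y + k²(λ0² + λ1²)] / (λ0 − λ1)²

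- Bracket: 0.0884/2000 + 0.0225 × 0.004029 = 0.0000442 + 0.0000907 = 0.0001349.
- (λ0 − λ1)² = 0.0156² = 0.0002434.
- c = 7: √(5 × 0.0002434/0.0001349) = 3.004; 3.004 − 1.960 = 1.044; power 85.2 %. The protocol states "30 % incidence reduction with 85.3 % power", and all 12 cells of Table 1 reproduce within 0.3 points on this basis.
- c = 14, the number of pairs actually randomised: power 99.6 %. (That Table 1 fits seven pairs and not 14 is a separate matter.)

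The power table is therefore a matched-pair calculation.

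**2. What cancels in the crossover.** Let D be a cluster's log rate in the first intervention period minus that in the second. Any effect that is constant over time, including a constant pair effect, drops out of D. Only period-specific variation shared by the pair can make the pairing matter. If the D values of two paired clusters have correlation r, the variance of their difference is 2·Var(D)·(1 − r), while an unpaired analysis uses 2·Var(D). Its standard error is too large by 1/√(1 − r), never too small.

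Example. Assumptions not in the protocol: 80 % of the cluster variance is constant over time, half of the remainder is shared by the pair, and each period lasts 16 months.
- Log-scale cluster variance at CV 0.15: ln(1 + 0.15²) = 0.02225. Period-specific part: 0.2 × 0.02225 = 0.00445.
- Poisson part: 1/(0.052 × 2000 × 16/12) = 0.00721.
- r = 0.5 × 0.00445/(0.00445 + 0.00721) = 0.191. Inflation of the standard error: 1/√0.809 = 1.11.
- A nominal 5 % z test then rejects when |Z| > 1.96 × 1.11 = 2.18, about 2.9 %, before any small-sample effect of the sandwich.

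**3. Simulation under no effect.** 28 clusters in 14 pairs, Poisson counts, independence-working Poisson GEE clustered on cluster, 2000 to 4000 runs in the main scenarios, CV 0.15 to 0.5. Rejection at nominal 5 %:

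| Crossover analysis | Pairs share no period variation | Pairs share half of it |
|---|---|---|
| Unpaired GEE, ordinary sandwich, z | 6.4 to 8.3 % | 2.5 to 4.5 % |
| Unpaired GEE, Kauermann-Carroll, t(26) | 4.2 to 6.3 % | 1.6 to 3.3 % |
| Unpaired GEE, Mancl-DeRouen, t(26) | 3.6 to 5.6 % | 1.3 to 2.6 % |
| Pair-level t, 13 df | 4.2 to 5.4 % | 4.8 to 5.4 % |

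A second, simpler simulation gave about 7 % and about 2 to 3.5 % for the first row, and about 5 % throughout for the last. Monte Carlo error is about 0.5 points. The simulations use cluster-period totals, with no age or months-since-intervention term.

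**4. Adding pair terms alone.** In a first-period parallel comparison (CV 0.15, pair share of variance 0.5, 300 runs), pair fixed effects with ordinary sandwich errors and z rejected about 20 %. With t(26), Kauermann-Carroll gave 6.0 % and Mancl-DeRouen 2.7 %.

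**The case against.** The best defence has four parts.

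**The article is condensed.** Finite-sample corrections are commonly left to an analysis plan, and none is shown. This stands. The absence of a small-sample correction cannot be asserted, because the text neither promises nor excludes one. It does not excuse the missing pair term: the section gives an itemised list of model terms for all endpoints, and the pairs are not in it.

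**The crossover makes each cluster its own control.** This stands for time-constant pair effects, which cancel. It does not cover variation shared by a pair within a period.

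**Baseline is already in the model.** Pairs were ranked mainly on clinical incidence, and the model includes the pre-intervention period and an arm indicator. These terms adjust for an average baseline difference between arms. They do not represent pairs.

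**Breaking the match is a recognised choice.** It can be, but then it should be stated and justified, and the sample size should not rest on pairs.

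Three stronger readings are tempting, and the documents support none of them.
- *Type I error exceeds 5 % because the pairing is ignored.* Step 2 shows the opposite direction. Any excess comes from an uncorrected sandwich, which is not stated.
- *The intervals are too narrow.* This is true only under that same unstated choice and without shared period variation. With shared variation they are too wide.
- *Power for a 30 % reduction falls from 99.6 % to about 80 %.* The lower figure needs an unmatched CV of 0.30, which the protocol nowhere gives, and a parallel comparison instead of the planned crossover: √(13 × 0.0002434/0.0004068) − 1.960 = 0.829, or 79.6 %. At the stated CV of 0.15 the unmatched formula gives √(13 × 0.0002434/0.0001349) − 1.960 = 2.884, or 99.8 %, so there is no loss.

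**Conclusion.** The mismatch is real and can be read from the text: matched pairs within county in the randomisation and the sample size, and no pair or county in the models. Its consequence is uncertain calibration and possible loss of precision. It is not a demonstrated inflation of type I error.

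The unpaired crossover test may reject about 2 to 4.5 % of the time when pairs share half of the period-specific variation. It may reject about 6.4 to 8.3 % when they share none and an ordinary sandwich with a normal reference is used. These ranges rest on assumed within-pair correlations and variance shares, because the protocol gives none. A standard correction largely removes the liberal excess but makes the conservative case more conservative. The pair-level test stayed close to 5 % in every crossover scenario examined. The point should be addressed, but it does not undermine the trial.

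**What to change.** Make the primary test a pair-level crossover analysis. For each of the 14 pairs, take the first-period minus second-period log rate in the cluster treated first, and subtract the same quantity for the cluster treated second. Half the mean of these contrasts estimates the log rate ratio. Test it by t on 13 degrees of freedom, or by permutation over the 2^14 = 16,384 within-pair allocations. County is absorbed because pairs are nested in it.

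Alternatively, keep the GEE, add pair nested in county, and specify bias-corrected sandwich errors (Mancl-DeRouen or Kauermann-Carroll) with a t reference. Pair fixed effects without such a correction should not be used. In either case, state the variance estimator and reference distribution, and use the same approach for vector density and EIR. If the sponsor prefers to ignore the pairs, the protocol should say so and justify it.

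The cost is a change of wording before the year 5 analysis, with no effect on field work. The downside is fewer degrees of freedom and possibly slightly wider intervals if pairing proves ineffective.

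### The Data analysis section does not say which estimate decides the primary comparison, and keeping months since intervention in the same model could hide an effect that builds up

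*Protocol article*

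**What the plan says.** All of the relevant text is in the Data analysis section of the protocol article, apart from the sample size.

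- Clinical incidence is analysed by Poisson regression with GEE on monthly grouped data, with intervention, age and calendar time as covariates. "Intervention will be a time-varying covariate since the treatment crosses over after three intervention rounds".
- One odds ratio with a 95 % interval, treatment against control, is promised for clinical malaria.
- After the vector density and EIR models are introduced, the text turns to all the analyses together: "clusters will be indicated as intervention and control, calendar time will be categorized into" seven named periods. Months since intervention, for the first intervention and for the crossover, is a further independent variable.
- The purpose is then given: "These variables will allow for comparison between intervention and control clusters based on baseline observations, e.g., relative reduction in vector density". The same sentence says the variables allow a cumulative effect to be evaluated, for example a second round adding to the first.

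The Sample size justification describes a single matched-pair comparison "to detect a 50 % protective efficacy conferred by the treatment compared with the reference group (no treatment").

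**The concern.** These sentences describe different quantities. A time-varying indicator gives one effect that changes arm at crossover and pools both halves. A cluster label combined with periods gives comparisons of the two cluster groups against baseline, one per period. After crossover a fixed label no longer matches exposure. A months-since-intervention term changes the meaning of the intervention coefficient, because it becomes the effect when months since intervention equals zero.

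The second set of terms is said to apply to all the analyses, so it reaches the primary endpoint. Nothing says which term produces the one estimate that is promised. The trial is open-label and is analysed in year 5, when every candidate estimate can be computed. Two things are at stake:

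- A real effect that grows over rounds could be read from the wrong coefficient and missed.
- The deciding contrast could be settled after the data are known.

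**Working it through.** **1. Does the sample size identify the contrast?** The inputs are "52 clinic cases per 1000 population year", "a two-tailed alpha with a human population size of 2000 per cluster" and a between-cluster coefficient of variation k of 0.15. The matched-pair formula with c pairs gives

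power = Φ(√{(c−2)(r0−r1)² / [(r0+r1)/y + k²(r0²+r1²)]} − 1.96).

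For a 30 % reduction, r0 = 0.052, r1 = 0.0364, y = 2000 and c = 7:
- (r0−r1)² = 0.00024336
- (r0+r1)/y = 0.0000442
- k²(r0²+r1²) = 0.0225 × 0.00402896 = 0.00009065
- 5 × 0.00024336 / 0.00013485 = 9.02, whose root is 3.00
- power = Φ(1.04) = 85.2 %, against 85.3 % in Table 1.

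The other entries also reproduce, for example 98.6 % against 98.7 % and 48.4 % against 48.6 %. The powered test is therefore one parallel paired comparison that uses neither the crossover nor the baseline. It does not identify the contrast.

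**2. What the months-since term does.** Three rounds at 4-month intervals give 12 treated months, t = 1 to 12. Assume that the log rate ratio builds linearly to ln 0.70 = −0.357 at month 8 and then stays there. The fraction reached is f(t) = min(t/8, 1).
- Intervention indicator alone: mean f = 8.5/12 = 0.708, so the rate ratio is exp(−0.357 × 0.708) = 0.78.
- Indicator plus linear months since intervention (zero when untreated): slope = (67.5 − 6.5 × 8.5)/143 = 0.0857. Intercept = 0.708 − 6.5 × 0.0857 = 0.152. The intervention coefficient is exp(−0.357 × 0.152) = 0.95.

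A Poisson GEE simulation (28 clusters, 8-month build-up, cluster-by-period SD 0.15, both assumed) agrees. It gives 0.77 with power about 100 % without the term, and 0.94 with power about 17 % with it.

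Two limits follow from the algebra. If the effect is constant from the first month, f(t) = 1, the slope is 0 and the coefficient is not shifted. If months since intervention were coded identically in both arms, it would be a function of calendar time only and would leave the arm contrast alone. The stated aim of evaluating a cumulative effect points to time on larvicide instead.

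**3. Error rate if any contrast could be used.** This is a null simulation with 60,000 runs, 14 clusters per arm, a 10-month baseline, 12-month intervention periods, 4-month post-intervention periods, and t tests on cluster log rates. The share of variance at cluster-by-period level was varied from 0 to 1.

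| Accepted if any is significant | Two-sided error | Favouring larvicide only (nominal 2.5 %) |
|---|---|---|
| Any one contrast alone | 4.8 to 5.3 % | – |
| Time-varying plus one period contrast | about 9.2 % (8.3 to 9.6 %) | about 4.5 % |
| Time-varying plus both intervention periods | about 12.4 % (11.6 to 12.6 %) | about 6.6 % |
| Five, with both post-intervention periods | 18.7 to 20.2 % | about 11 % |

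Independent tests would give 1 − 0.95² = 9.75 % for two and 1 − 0.95⁵ = 22.6 % for five.

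**4. Would the candidates disagree?** Expected cases are 2000 × 0.052 = 104 per cluster-year. With an assumed cluster-by-period SD s of 0.10 to 0.20 and periods of equal length, each cluster-period log rate has variance v = s² + 1/104, apart from the permanent cluster effect.
- First half minus baseline: SE = √(2v × 2/14) = 0.075 to 0.119.
- Pooled crossover, half of (first half minus second half): half of that, 0.037 to 0.060.

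At a 20 % reduction, simulated power is 43 to 80 % for the first-half contrast and 95 to 100 % for the pooled one, and the two disagree in 20 to 53 % of trials. Taking the first-half SE as 0.08 to 0.12, a normal approximation gives power of about 84 to 99 % at 30 % (0.357/0.12 = 2.97; 0.357/0.08 = 4.46). At the 50 % design effect it is above 99.9 % (0.693/0.12 = 5.78), so disagreement there would be rare.

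**The case against.** The section can be read as having one primary contrast. It opens with the incidence model, makes intervention time-varying and promises one estimate. The coding of labels and periods comes only after the vector models, and the only worked example of a baseline comparison is vector density, a secondary endpoint. No group-by-period interaction is written; it has to be inferred. The crossover is a declared design feature, which favours the pooled effect. A cluster-group term beside a time-varying exposure is a legitimate adjustment. A condensed article may also leave the ranking of contrasts to an analysis plan that is not shown.

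Most of this stands. A reader might infer that the plan's false-positive rate is 9 to 20 %. The document does not support that: it states no rule that success on any contrast suffices, it gives no number of contrasts, and each contrast alone holds about 5 %. A reader might also infer that the cluster label must be removed, which does not follow. The low power of the baseline-relative contrast matters mainly for effects below the 50 % target.

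One part is not answered. The article itself places months since intervention in all the analyses, including the primary one. Even a reader who takes the time-varying term as primary then cannot tell whether the reported figure is an average effect or an effect at month zero.

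**Conclusion.** The point holds as a defect in what the section states. The deciding estimate is not identified, and the model as written can turn the intervention coefficient into a month-zero effect while the same section anticipates that effects may accumulate. Under a build-up over eight months to a 30 % reduction, the coefficient would show a reduction of about 6 % instead of about 23 %, and power would fall from about 100 % to about 17 %. This rests on three assumptions: the build-up shape, the cluster-by-period SD of 0.15, and coding of the term as time on treatment. With an immediate constant effect the coefficient would not be shifted.

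The error inflation is a conditional risk only: about 9 to 20 % two-sided, or about 4.5 to 11 % against 2.5 % in the favourable direction, if two to five contrasts were all open to choice.

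**What to change.** State in the Data analysis section, or in the analysis plan, that:

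- The trial is decided by the rate ratio for the time-varying intervention indicator on clinical malaria incidence, pooled over both crossover halves and tested two-sided at 5 %.
- The periods that enter this estimate are listed, including how the post-intervention months count. The section currently excludes the second four months of the washout yet lists a four-month washout among the calendar categories.
- The model adjusts for calendar period and age. The cluster-group term may stay. Months since intervention is left out.
- Period-versus-baseline contrasts, and the months-since-intervention or cumulative effect, are secondary estimates with 95 % intervals and do not replace the pooled result.

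The cost is a few sentences and no new data. The small downside is that an effect confined to one period can no longer be claimed as the primary result.
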